### Strategies to improve adherence to interventions {11c} {18b}

Avoiding the development of extensive drug resistance (resistance to any fluoroquinolone plus BDQ or LZD, in addition to RR-TB) is a priority. Since AE, particularly gastrointestinal, are frequent due to the high number of tablets, directly observed treatment (DOT) is compulsory throughout the duration of treatment. DOT is planned and implemented in close consultation with the patient and family so that an appropriate person to support the patient is identified, trained and supervised. All AE are clearly explained to patients and adequately treated and documented in their patient treatment cards. Ambulatory treatment is strongly recommended from the start of treatment (or as soon as possible) because it is more cost-effective than hospitalisation and it is often more acceptable to patients [17, 18]. Patient preferences and barriers such as long distances between the patient’s home and the health centre, transportation costs, incompatibilities of the centre’s opening hours with the service hours, etc., are assessed to adapt the service to the patient’s needs and improve adherence to treatment. Social support (reimbursement of daily transport costs for ambulatory treatment and nutritional support) is part of patient care. At least one visit is organised per patient, and as under routine care, the patient's home is visited by clinic staff at the beginning of the treatment, to better understand the patient’s living conditions, to be able to trace the home in a later phase, and to investigate those who are in close contact with the patient. Patients who delay for their appointment are contacted the same day or the next day, if possible first by phone. If this is not possible, a home visit is organised to explore why the patient was delayed, to prevent further irregularities, and to reinforce adherence to treatment.

### Relevant concomitant care permitted or prohibited during the trial {11d}

In RR-TB patients co-infected with HIV and on antiretroviral drugs we take into account the following measures:Tenofovir and SLID: strict monitoring of kidney function.Atazanavir and LZD: strict monitoring of the hemogram.Efavirenz (inducer of CYP3A4, thus decreases the concentration of BDQ) should not be used with BDQ.Protease inhibitors (inhibitors of CYP3A4, thus increase the concentration of BDQ) and BDQ can be used together with caution.Nevirapine and BDQ can be used together without problems

### Provisions for post-trial care {30}

In case of treatment failure or relapse sputum samples are sent to the ITM in Antwerp for DST. The National RR-TB Committee will construct a RR-TB retreatment regimen taking into account DST results. RR-TB retreatment will be provided while assuring the same level of quality of care as during the trial. This includes the continuation of the best possible TB treatment as long as needed, following national TB guidelines, and also care of any AE or complications.

### Outcomes {12}

Primary endpoint, as a measure of safety: any severe (grade 3–5) AE, with onset of symptoms before the end of treatment, and with the maximum grade measured up to 6 months after the end of treatment.

Secondary endpoints:As a measure of effectiveness: treatment outcome, with relapse-free success (cure or treatment completion without proof of relapse during 12 months of active post-treatment follow-up) as favourable outcome and treatment failure, relapse, lost to follow-up, and death as an unfavourable outcome.As a measure of adherence to the regimen: proportion of daily doses taken.

The definitions used to grade AE are based on French National Agency for Research on AIDS and hepatitis (ANRS) [19].

### Participant timeline {13}

Depending of the month of RR-TB diagnosis, as shown on the printed Xpert MTB/RIF result, the patient is enrolled on either the control or experimental treatment arm (a coin toss determines which regimen is used for which month). Each patient is treated for 9 to 11 months and is followed actively for 12 months after the end of treatment.

The inclusion assessment includes clinical, bacteriological, laboratory and additional tests described in Table 1.

**Table 1 Tab1:** Enrolment and assessments

		Enrolment	Treatment phase (M = month)											Follow-up		Close-out
			M 1	M 2	M 3	M 4	M 5	M 6	M 7	M 8	M 9	M 10	M 11	MF 6	MF 12	
Eligibility screening		X														
Written informed consent		X														
Allocation		X														
Assessment	Clinical examination	X	X	X	X	X	X	X	X	X	X	X*	X*	X	X	
	Treatment adherence		X	X	X	X	X	X	X	X	X	X*	X*			
	Sputum smear	X (2)	X	X	X	X (2)	X (2)*	X (2)*	X	X	X (2)	X(2)*	X (2)*	X	X	
	Bacteriological culture	X		X		X		X			X	X*	X*	X	X	
	SL-LPA (FQ/Injectables)	X												X±	X±	
	Haemoglobin/CBC#, creatinine@, potassium@, liver enzymes	X	X	X	X	X	X*	X*								
	Visual acuity, test for peripheral neuropathy, Audiometry@	X	X	X	X	X*	X*									
	Chest X-ray	X									X	X*	X*			
	ECG§	X		X		X		X		X		X*	X*			
Safety outcome evaluation													X	X		
Treatment outcome evaluation																X

*If the intensive phase is prolonged

**±** DST carried out at baseline, after reversion (positive culture after conversion) during treatment, and if bacteriological culture is positive during the 12-month post-treatment follow-up (with storage of the baseline, treatment failure or relapse strain for genotypic analysis)

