## Interventions

### Explanation for the choice of comparators {6b} and intervention description {11a}

The control arm relies on the Niger RR-TB treatment strategy. It relies on the national 9–11- month standard RR-TB STR, which includes moxifloxacin (MFX), CFZ, ethambutol (E), and pyrazinamide (Z) throughout, supplemented by a SLID (amikacin), prothionamide (PTO) and high-dose isoniazid (Hh; 10mg/kg) during the first 4 months (6 months if delayed conversion on smear microscopy at treatment month 4). The SLID is replaced with LZD in case of any hearing disturbance detected on audiometry (4-6 SLID-Hh-PTO-MFX-CFZ-E-Z/5 MFX-CFZ-E-Z, with LZD replacing the SLID in case of any hearing disturbance detected on audiometry, at baseline or during treatment).

In this control arm, the STR uses fluoroquinolone (moxifloxacin) as core drug, with both high bactericidal and sterilising activity. The SLID (or LZD if it replaces SLID) provides early bactericidal activity, and the other drugs add bactericidal or sterilising activity [16].

The experimental arm uses the WHO all-oral regimen, which contains LZD, high-dose isoniazid, prothionamide, high-dose levofloxacin (LFXh), BDQ, CFZ and pyrazinamide for 4 months (6 months if delayed conversion on smear microscopy at treatment month 4), followed by 5 months of treatment with high-dose levofloxacin, BDQ, CFZ and pyrazinamide (4-6 LZD-Hh-PTO-LFXh-BDQ-CFZ-Z/5 LFXh-BDQ-CFZ-Z).

BDQ and fluoroquinolone (levofloxacin) are used as core drugs, thus with high bactericidal and sterilising power. LZD, with good early bactericidal activity, protects BDQ and fluoroquinolone from the acquisition of resistance. The other drugs add bactericidal or sterilising activity [16].

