# To be done if the patient is taking linezolid

@ To be done if the patient is taking a second-line injectable drug

**§** A basic electrocardiogram (ECG) must be performed and additional ECGs done at weeks 1 and 2 after the start of treatment and then once a month during treatment. The ECGs must be repeated if necessary in the event of clinical suspicion of heart rhythm problems and conduction disorders, or other clinical signs (e.g. dehydration and electrolyte disorders)

Abbreviations: *CBC* complete blood count, *ECG* electrocardiogram, *FQ* fluoroquinolone, *M* month, *MF* month of follow-up after treatment completion, *SL-LPA* second-line line probe assay

Baseline sputum samples are systematically sent to the NRL and the ITM in Antwerp. However, as in any life-saving situation, treatment of drug-resistant tuberculosis is not withheld from a patient when DST results are not available. Hence the regimen may be modified once DST results become available {see 11b}.

All patients enrolled in the study undergo regular assessment of clinical and para-clinical parameters as described in Table 1. Monitoring procedures are adapted to fit the drugs used in either the control or experimental treatment arm (e.g. close monitoring of haemoglobin for patients taking LZD; monthly audiometry when a SLID is used).

Before starting treatment with linezolid, providers invite family members to collect blood bags to be able to do a timely blood transfusion in the event of bone marrow aplasia.

Every month sputum samples are collected for bacteriological monitoring using smear microscopy with auramine staining. In case of lack of conversion on smear microscopy at month four (two samples), the intensive phase is extended for one or 2 months maximally.

At month two, four, six and nine (10 or 11 if the intensive phase was prolonged with 1 or 2 months, respectively), samples are collected for culture. Post-treatment follow-up at 6 and 12 months after cure or treatment completion relies on smear microscopy and culture.

In the event of a treatment failure during treatment or relapse during the 12-month post-treatment follow-up, genotyping is done at the ITM in Antwerp on the baseline and failure/relapse sample to determine the strain identify and to distinguish between true treatment failure/relapse and reinfection.

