### Sample size {14}

A total of 230 patients will be included prospectively to compare treatment arms (115 patients for each) in order to be able to identify a correlation between the treatment arms and the occurrence of any grade 3–5 AE, assuming that the “hazard ratio” for developing a grade 3-5 AE is 3.2 times higher among patients in the experimental treatment arm (WHO all-oral regimen) compared to the control arm (STR that contains either a SLID or LZD; 5% vs 15%; with power 0.8, alpha 0.05).

Justification of assumptions :Of the 153 patients already treated according to the Niger RR-TB treatment strategy, with LZD replacing the SLID in the STR in case of ototoxicity and with monthly audiometry, 6 (3.9%) had an AE of degree 3–5 [15]. For the calculation of the sample size, a “conservative” estimate of 5% was used.Of the 33 patients treated with linezolid instead of the SLID in case of ototoxicity, 6 (18.2%) had grade 3–5 AE [15]. A “conservative” estimate of 15% was used to calculate the sample size.

In addition to the prospective treatment arms, a retrospective cohort of 255 patients enrolled on treatment between 2017 and April 2021 will be used during an interim analysis (see interim analysis), if characteristics known to affect the treatment outcome of the retrospective cohort are not significantly different from the prospective arms, and in case the proportion with a grade 3-5 adverse event is not significantly different between the retrospective cohort and those prospectively treated using the Niger RR-TB treatment strategy (SLID-containing regimen, with LZD replacing the SLID in case of ototoxicity).

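### Table 1 schedules vision and neuropathy testing one column earlier than the blood tests, so 4- and 6-month linezolid courses end without one; a minor, cheaply closed gap that may be deliberate

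*Protocol article*

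**What the plan says.** All references are to the protocol article. Under Explanation for the choice of comparators {6b} and intervention description {11a}, the control arm receives the injectable "during the first 4 months (6 months if delayed conversion on smear microscopy at treatment month 4"), with linezolid taking its place if hearing is disturbed. The experimental arm receives linezolid for the same 4 to 6 months. Participant timeline {13} bases prolongation on the month-four smear: without conversion, "the intensive phase is extended for one or 2 months maximally".

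Two rows of Table 1 matter here:

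- "Visual acuity, test for peripheral neuropathy, Audiometry": enrolment, M1, M2, M3, M4*, M5*, then blank through the 12-month follow-up visit.
- "Haemoglobin/CBC#, creatinine@, potassium@, liver enzymes": enrolment, M1, M2, M3, M4, M5*, M6*.

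The asterisk restricts a test to patients with a prolonged intensive phase. Creatinine, potassium and audiometry all carry the mark @, explained as "To be done if the patient is taking a second-line injectable drug". Visual acuity and neuropathy testing carry no drug-specific mark. The text below the table gives, as an example of drug-adapted monitoring, "monthly audiometry when a SLID is used". It has no corresponding sentence for vision or neuropathy.

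**The concern.** The two rows monitor toxicity of the same drugs over the same exposure period, yet their schedules differ by one column. Three tests share the mark @; two of them are due at M4 for every injectable patient and at M6 if prolonged, while audiometry is due at M4 only if prolonged and has no mark at M6.

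The stake is how adverse events are ascertained. The primary endpoint is any grade 3–5 event in a trial where clinicians and patients know the regimen. The Secondary analysis section adds a Cox model of injectable against linezolid that names four toxicities; this row tests for three of them (ototoxicity, optic neuritis, neurological disorders). Toxicity arising in the last exposure month would come to light through symptoms, questioning or general examination rather than a scheduled test, and might be graded later. Under Primary analysis, Cox follow-up ends on the grading date, so late grading could move event times.

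**Working it through.** No figure in the plan needs reproducing; the check is a mapping of the schedule.

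**1. Is the offset an extraction artefact?** The header needs 15 cells (enrolment, M1–M11, two follow-up visits, close-out). The seven assessment rows checked each have exactly 15, so no cell was lost from this row.

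**2. Which on-treatment tests fall due, by length of the intensive phase?** Starred marks are dropped for a 4-month course, and visits after the end of exposure are not counted.

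| Intensive phase | Vision/neuropathy/audiometry row | Blood row | Last test in the first row |
|---|---|---|---|
| 4 months | M1–M3 | M1–M4 | M3 |
| 5 months | M1–M5 | M1–M5 | M5 |
| 6 months | M1–M5 | M1–M6 | M5 |

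**3. Number of tests, including enrolment.**

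- As printed: 1+3 = 4 for 4 months; 1+3+2 = 6 for 5 months; 1+3+2 = 6 for 6 months.
- With the blood-row pattern: 1+4 = 5; 1+4+1 = 6; 1+4+2 = 7.
- The difference is one test set for a 4- or 6-month course and none for a 5-month course.

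**4. What else is scheduled at M4 and M6?** Table 1 has clinical examination at every treatment month and blood tests at M4 and M6*. The text has adverse events asked about at each visit, and Plans for assessment {18a} has monthly screening by trained staff. For hearing, "monthly audiometry when a SLID is used" applies on top of the table, and the Background describes audiometry at baseline and monthly in the Niger strategy. Nothing equivalent is stated for visual acuity or neuropathy.

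**5. How many patients could be concerned?** Sample size {14} gives two counts: "Of the 153 patients already treated according to the Niger RR-TB treatment strategy" and "Of the 33 patients treated with linezolid instead of the SLID in case of ototoxicity". Assuming the 33 are a subset of the 153:

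- Switch share: 33/153 = 21.6% (Wilson 95% CI 15.8% to 28.7%).
- Controls on linezolid: 115 × 0.216 = 24.8, about 25 (115 × 0.158 = 18 to 115 × 0.287 = 33).
- All linezolid patients: 115 + 25 = about 140 (133 to 148) of the planned 230.
- Controls staying on an injectable: 115 × (1 − 0.216) = about 90 (82 to 97). For them the open item is audiometry, which the text largely covers.

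These figures count people taking a drug, not events missed or misdated. They are upper bounds, because patients prolonged by exactly one month have no gap and their share is not given. The ranges carry only the uncertainty in the switch proportion, not the sampling variation of a new group of 115.

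**The case against.** The strongest reply is that the row is coherent as printed. If M4 means the end of month 4, as the month-four smear decision and the end-of-treatment tests at M9 suggest, then enrolment, M1, M2 and M3 give one test before each of exposure months 1 to 4, and M4* and M5* come before months 5 and 6. Audiometry guides the switch to linezolid, and a patient stopping at month 4 has no switch left to decide. This stands as a possible rationale. A reader might infer that M4* contradicts its own footnote and must be a misprint; that does not follow, because prolongation is decided at M4 itself. The rationale is not stated, however, and creatinine and potassium, which share the mark @, do not follow it. These tests also help to measure a safety endpoint, a purpose that does not end with the last dosing decision.

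A reader might also infer that hearing goes unmonitored at the end of injectable treatment, or that 4- and 6-month courses end with no scheduled test at all. The documents support neither, given the monthly audiometry sentence and the assessments in step 4 of the check. The audiometry sentence would conflict with the table only if M4 is a visit within month 4.

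Lastly, a reader might infer a biased safety comparison. Table 2 defines grade 3 by limitation of usual activity and need for intervention, so such events would mostly show themselves at monthly contacts. Table 1 also has safety outcome evaluations at M11 and at the 6-month follow-up, the worst grade is taken through six months post-treatment, and the chi-square or Fisher comparison does not use the grading date. All of this stands and limits the consequence to possible late detection or grading.

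**Conclusion.** The point holds in a narrow form and is minor. Table 1 has no visual acuity or peripheral neuropathy test at the end of a 4- or 6-month linezolid course, and none afterwards. This touches the experimental arm and those controls switched to linezolid: one test set per affected patient, at most about 140 patients on the subset assumption. It is a weakness in safety monitoring and event ascertainment that is cheap to close, not a demonstrated error, since the row can be read as deliberate. The document gives no event rate for the last exposure month and no share of prolonged courses, so neither the size nor the direction of any effect on the Cox models can be derived.

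**What to change.** Mark the row at enrolment, M1, M2, M3, M4, M5* and M6*, as in the blood-test row. Two cells change: M4 loses its asterisk and M6* is added; M5* stays. State that audiometry is for patients on an injectable in that month, and visual acuity and neuropathy testing at least for patients on linezolid in that month, so that every course length ends with a test in its last exposure month. If sites already test at these visits, correcting the table is enough.

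The cost is one extra set of bedside tests, and a little clinic time, at a visit that already takes place: M4 for a 4-month course or M6 for a 6-month course. If the present pattern is intended, one sentence giving the reason would settle the ambiguity but would leave the end-of-linezolid gap in place.

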# To be done if the patient is taking linezolid

@ To be done if the patient is taking a second-line injectable drug

**§** A basic electrocardiogram (ECG) must be performed and additional ECGs done at weeks 1 and 2 after the start of treatment and then once a month during treatment. The ECGs must be repeated if necessary in the event of clinical suspicion of heart rhythm problems and conduction disorders, or other clinical signs (e.g. dehydration and electrolyte disorders)

Abbreviations: *CBC* complete blood count, *ECG* electrocardiogram, *FQ* fluoroquinolone, *M* month, *MF* month of follow-up after treatment completion, *SL-LPA* second-line line probe assay

Baseline sputum samples are systematically sent to the NRL and the ITM in Antwerp. However, as in any life-saving situation, treatment of drug-resistant tuberculosis is not withheld from a patient when DST results are not available. Hence the regimen may be modified once DST results become available {see 11b}.

All patients enrolled in the study undergo regular assessment of clinical and para-clinical parameters as described in Table 1. Monitoring procedures are adapted to fit the drugs used in either the control or experimental treatment arm (e.g. close monitoring of haemoglobin for patients taking LZD; monthly audiometry when a SLID is used).

Before starting treatment with linezolid, providers invite family members to collect blood bags to be able to do a timely blood transfusion in the event of bone marrow aplasia.

Every month sputum samples are collected for bacteriological monitoring using smear microscopy with auramine staining. In case of lack of conversion on smear microscopy at month four (two samples), the intensive phase is extended for one or 2 months maximally.

At month two, four, six and nine (10 or 11 if the intensive phase was prolonged with 1 or 2 months, respectively), samples are collected for culture. Post-treatment follow-up at 6 and 12 months after cure or treatment completion relies on smear microscopy and culture.

In the event of a treatment failure during treatment or relapse during the 12-month post-treatment follow-up, genotyping is done at the ITM in Antwerp on the baseline and failure/relapse sample to determine the strain identify and to distinguish between true treatment failure/relapse and reinfection.

At each visit, patients are asked about AE and all responses are recorded in the patient's file. Patients are advised to consult study staff in case AE occur between scheduled visits. If patients present with an AE or other problems requiring specific examinations between scheduled intervals, the frequency of monitoring and supervision will be adjusted.Patients on RR-TB treatment receive DOT during consultations at the TB clinic (thus physical site visits), which allows for regular screening of AE, with early referral to a medical doctor in case a severe AE is identified.Medical care is provided by nurses at the TB centres, with easy access to referral consultations by medical doctors and hospitalisation.Patients are informed to consult a TB nurse in case a new symptom emerges, or in case an existing symptom worsens.Patients living far from RR-TB Units stay in close contact by phone. Moreover, the nurse discusses whether visits can be spaced (for instance, from daily to weekly), and which days and hours convene best for the patient to come to the clinic.Transport costs are reimbursed, as in routine care.

### Sample size {14}

A total of 230 patients will be included prospectively to compare treatment arms (115 patients for each) in order to be able to identify a correlation between the treatment arms and the occurrence of any grade 3–5 AE, assuming that the “hazard ratio” for developing a grade 3-5 AE is 3.2 times higher among patients in the experimental treatment arm (WHO all-oral regimen) compared to the control arm (STR that contains either a SLID or LZD; 5% vs 15%; with power 0.8, alpha 0.05).

Justification of assumptions :Of the 153 patients already treated according to the Niger RR-TB treatment strategy, with LZD replacing the SLID in the STR in case of ototoxicity and with monthly audiometry, 6 (3.9%) had an AE of degree 3–5 [15]. For the calculation of the sample size, a “conservative” estimate of 5% was used.Of the 33 patients treated with linezolid instead of the SLID in case of ototoxicity, 6 (18.2%) had grade 3–5 AE [15]. A “conservative” estimate of 15% was used to calculate the sample size.

In addition to the prospective treatment arms, a retrospective cohort of 255 patients enrolled on treatment between 2017 and April 2021 will be used during an interim analysis (see interim analysis), if characteristics known to affect the treatment outcome of the retrospective cohort are not significantly different from the prospective arms, and in case the proportion with a grade 3-5 adverse event is not significantly different between the retrospective cohort and those prospectively treated using the Niger RR-TB treatment strategy (SLID-containing regimen, with LZD replacing the SLID in case of ototoxicity).

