### Trial design {8}

This is a pragmatic randomised clinical trial using stratified block randomisation to compare the safety, effectiveness and adherence of an experimental arm, the WHO all-oral regimen, including BDQ and LZD for all, with the control arm, the Niger RR-TB treatment strategy, using a STR that contains either a SLID or LZD, depending on the presence of audiometry abnormalities. We hypothesise that the STR that contains either a SLID or LZD is more safe, thus superior, than the WHO all-oral regimen, with LZD for all.

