## Statistical methods

### Statistical methods for primary and secondary outcomes {20a}

#### Primary analysis

The proportion of patients with grade 3–5 AE will be compared between the experimental treatment arm and the control arm using a chi-square test (or exact Fisher test). A Cox regression model will be developed to measure the association between enrolment in either the experimental or control arm and the incidence of a grade 3–5 AE. All patients who started treatment will be included. The start of follow-up time will be the date of start of treatment. The end of follow-up time will be the date an AE was graded as grade 3–5. In patients without AE, the date of the end of treatment will be used if they were cured or completed treatment, or the date of the last visit in case the patient was lost to follow-up before ending the treatment, or the date of death in case the patient died during treatment.

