Second, we will conduct interim analyses to stop enrolment early in case the primary safety endpoint would be significantly more frequent in one of both arms. For the interim analysis, we will also consider including data from a retrospective cohort of patients treated in precisely the same way as in the control arm, in terms of treatment and monitoring procedures, including consent procedures and prospective collection of safety and treatment response data. We will verify whether the characteristics of the retrospective cohort are significantly different from those of the RCT cohort and whether the proportion with a grade 3–5 adverse event is significantly different between the retrospective cohort and those prospectively treated using the Niger RR-TB treatment strategy (SLID-containing regimen, with LZD replacing the SLID in case of ototoxicity). If not different, data from the retrospective cohort will be used. As such we aim to avoid a too long enrolment period and important delays between this study and informing national and international treatment guidelines. A previous analysis showed a higher rate of grade 3-5 adverse events in a small observational cohort of patients treated with a LZD-containing STR compared to the SLID-containing STR. With our trial, we therefore hypothesise that the risk of severe adverse events is higher among patients treated with the newly recommended WHO all-oral regimen, with LZD for all, compared to the control arm, with a STR that contains either SLID or LZD. If indeed, the new WHO all-oral regimen shows to cause more adverse drug reactions, it would ethically not be justified to expose more patients than needed to this regimen, especially considering the exceptionally good results obtained with the control arm in our setting.

The findings of our trial will immediately inform the implementation of RR-TB treatment by the Niger NTP. All RR-TB sites are involved, thus findings are generalisable to the reality of Niger. The NTP director is involved as a co-investigator and thus can guide the implementation of recommendations informed by our findings. Our findings will also inform the international debate on the balance between striving towards a RR-TB treatment regimen that is both safe and effective.

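### With 115 patients per arm, neither primary analysis reaches the stated 80% power for 5% vs 15%; two-sided power is about 71–75%

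*Protocol article*

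**What the plan says.** Sample size {14} sets the number: "A total of 230 patients will be included prospectively to compare treatment arms (115 patients for each". The target effect is a hazard for a grade 3–5 adverse event that "is 3.2 times higher among patients in the experimental treatment arm", with the matching rates and error levels given in the words "compared to the control arm (STR that contains either a SLID or LZD; 5% vs 15%; with power 0.8, alpha 0.05". The section names neither the formula nor whether alpha is one- or two-sided.

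Primary analysis, under Statistical methods {20a}, gives two comparisons of the same endpoint. First, the proportions with a grade 3–5 event "will be compared between the experimental treatment arm and the control arm using a chi-square test (or exact Fisher test". Second, a Cox model for the effect of arm on time to such an event, in all patients who started treatment. The section does not say which of the two decides the trial.

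Two passages bear on sidedness. Trial design {8} states a directional hypothesis, that the control strategy "is more safe, thus superior, than the WHO all-oral regimen". The Discussion says enrolment would stop early "in case the primary safety endpoint would be significantly more frequent in one of both arms".

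**The concern.** A stated power is a claim about what the planned test will do under the planned rates. Here the sample size is framed on a hazard ratio, but the first-listed test compares proportions, and the usual two-proportion formula for 5% vs 15% asks for clearly more than 115 per arm. With only about 23 expected events and a hazard ratio above 3, it also has to be checked whether the events formula behind 230 is accurate for the Cox model itself.

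At stake is the chance of missing a threefold difference in severe adverse events, which is the trial's primary question. If that chance is well above 20%, readers will credit a non-significant result with more assurance than the design gives. With so few events, the two comparisons could also fall on opposite sides of 0.05, and the article gives no rule for that case.

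**Working it through.** **Inputs, all from Sample size {14}:** 115 per arm, 1:1; control 5%, experimental 15%, average 10%; hazard ratio 3.2; power 0.80; alpha 0.05, taken as two-sided. Normal quantiles are 1.960 and 0.842. The rates and the hazard ratio agree under proportional hazards: ln(0.85)/ln(0.95) = 3.17.

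**1. The plan's own figure (Schoenfeld).**
- Events = 4 × (1.960 + 0.842)² / (ln 3.2)² = 23.2.
- N = 23.2 / 0.10 = 232, against the stated 230.
- Expected events with 230 patients: 230 × 0.10 = 23. Power at 23 events = Φ(√23 × ln 3.2 / 2 − 1.960) = 79.6%.

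The stated number and power reproduce.

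**2. A second standard events formula (Freedman).**
- Events = (1.960 + 0.842)² × (4.2/2.2)² = 28.6, so N = 286.
- Power at 23 events = Φ(√23 × 2.2/4.2 − 1.960) = 71%.

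A gap this wide between two standard formulas shows that the approximation matters here.

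**3. Cox model by simulation.** Exponential event times, the same fixed follow-up for all, no dropout, 115 per arm, 5% vs 15%, 40,000 runs, about 23 events per run:

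| Cox test | Power |
|---|---|
| Wald | 70.8% |
| Score (log-rank) | 73.6% |
| Likelihood ratio | 74.6% |

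With the hazard ratio at exactly 3.2 these become 71.7%, 74.5% and 75.4%. About 131–140 per arm would be needed for 80%, depending on the statistic.

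**4. Chi-square test.**
- n per arm = [1.960 × √(2 × 0.10 × 0.90) + 0.842 × √(0.05 × 0.95 + 0.15 × 0.85)]² / 0.10² = 140.1, so 141.
- Power at 115 = Φ([0.10 × √115 − 1.960 × √0.18] / √0.175) = 71.8%.
- Exact enumeration of both binomials gives 74.5%; about 134 per arm would give 80%.

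**5. Fisher's exact test.** Exact enumeration at 115 per arm gives 64.9%.

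**6. The difference for which 115 per arm gives 80%,** control rate 5%, same methods (Cox: 20,000 runs):

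| Experimental rate | Chi-square, formula | Chi-square, exact | Cox Wald | Cox score | Cox likelihood ratio |
|---|---|---|---|---|---|
| 16% | 78.0% | 80.7% | 77.7% | 80.1% | 80.8% |
| 16.5% | 80.8% | 83.3% | 80.6% | 82.8% | 83.3% |

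So 80% is reached between about 16% and 16.5%, depending on the statistic.

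**7. Sidedness.** At one-sided 0.05 the chi-square formula gives 81.5% at 115 per arm (111 needed).

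**The case against.** **The calculation is standard and correctly reported.** This stands. The section is framed on a hazard ratio, so it belongs to the Cox model, and Schoenfeld's formula returns 232. A reader might infer an arithmetic error; step 1 shows there is none. The defect is that the approximation overstates the power of the test that will be run.

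**The Cox shortfall depends on simulation assumptions.** Partly right. Constant hazards, common follow-up and no dropout are assumptions of this check, not of the protocol. But Freedman's formula gives the same 71% without simulation, and the chi-square shortfall needs no event-time assumption.

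**The test may be meant as one-sided.** The hypothesis is directional, and a one-sided chi-square would reach 81.5%. But no one-sided test is stated, the stopping language refers to either arm, and 230 matches the two-sided Schoenfeld result (the one-sided one gives about 183). The one-sided reading is not supported.

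**The rates already carry a margin.** Sample size {14} calls both rates conservative against observed 6/153 (3.9%) and 6/33 (18.2%). At the observed rates, chi-square power at 115 per arm is 94% by formula and 96% exact. This is a fair mitigating point, although 33 patients give an imprecise estimate. It does not make the 80% true for the rates to which the protocol attaches it.

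**Stronger readings that the documents do not support.** One might quote Fisher's 65% as the trial's power, with a 35% chance of a miss. The wording "using a chi-square test (or exact Fisher test" reads as the usual fallback for small cells. Under the conventional rule of expected counts below 5, it would apply only with fewer than 10 events in total, a probability of about 0.04% under 5% vs 15%. One might also subtract power for loss to follow-up, but the article gives no loss rate, and all patients who start treatment are analysed. Nor does it say that a null result would be read as equal safety: the Abstract and Discussion make replacing the Niger strategy conditional on evidence favouring the all-oral regimen.

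**Conclusion.** The concern holds as a correction to a stated design property. At 115 per arm, 5% vs 15%, two-sided 0.05 and one final test, power is about 72–74% for chi-square and about 71–75% for Cox, some 5 to 9 points below the stated 80%. The probability of missing the assumed difference is about 25–29% instead of 20%. Fisher's 65% would apply only if that fallback were used.

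The conclusion rests on a two-sided reading of alpha, which the article does not state but its stopping language and the match to 230 both favour. The Cox figures also rest on the simulation assumptions above. None of the figures includes the two interim looks described under Interim analyses {21b}, so they describe a single final test and not the operating characteristics of the whole design.

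**What to change.** Keep 230 patients. In Sample size {14}, state that alpha is two-sided, name the method behind the number, and replace the 80% claim with wording such as: 115 per arm gives about 71–75% power for 5% vs 15%, and 80% power for about 5% vs 16–16.5%, for a single final test.

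In Primary analysis, name one deciding test. The Cox comparison is the natural choice because the sample size is framed on the hazard ratio. State which Cox statistic gives the p-value, since Wald and likelihood ratio differ by about 4 points of power here. Report the chi-square or Fisher comparison as supportive.

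The cost is a short text change in two sections and a less favourable stated power. Enrolment, follow-up and data collection do not change. If 80% at 5% vs 15% is regarded as essential, the alternative is to enrol more: about 131–140 per arm for Cox, or 134 (exact) to 141 (formula) for chi-square.
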